#### 2.3.1. Sample Size Calculation

Since data on the application of phage therapy for MSI, CRS and sepsis are currently scarce, we are unable to perform a power analysis due to the absence of an objective effect size. The main aim of this registry is to obtain safety and efficacy data. Based on previously received requests for phage therapy, an estimated 150 patients will be included. Furthermore, within this patient population, approximately 75 will have a positive phagogram and can therefore be treated with phage therapy.

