### 2.6. Statistical Analysis

As the aim of this registry is mainly descriptive and exploratory, patient characteristics and outcomes recorded at standard-of-care scheduled follow-up assessments will be presented using simple summary statistics.

Categorical variables will be summarized using the frequency and percentage for each category. Continuous variables will be summarized using the mean, standard deviation, inter-quartile range and minimum and maximum values. These summary statistics will in addition be presented according to the clinically relevant categories; i.e., according to the treatment received.

Complications will be reported both at the patient and the AE level. Given the exploratory nature of this study, any results will have to be interpreted carefully.

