## 4. Conclusions

In conclusion, for the first time, the PHAGEFORCE study will enable us to evaluate the safety profile of the applied phage therapy protocols for three different routes of administration. Together with the efficacy data that will be collected, this can act as the foundation for future clinical studies. From a molecular microbiology perspective, this study will help us gain insight into phage–bacteria interactions and optimize future phage selection and cocktail design.

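### Section 2.6 breaks summaries down only by treatment received, so adverse-event and other shared summaries would mix three diseases and describe none of the three routes whose safety profile is promised

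*Protocol article*

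**What the plan says.** Section 2.6 opens with the premise "As the aim of this registry is mainly descriptive and exploratory" and plans simple summary statistics. "Categorical variables will be summarized using the frequency and percentage for each category", and "Continuous variables will be summarized using the mean, standard deviation, inter-quartile range and minimum and maximum values". It then adds: "These summary statistics will in addition be presented according to the clinically relevant categories; i.e., according to the treatment received". On safety it says: "Complications will be reported both at the patient and the AE level". Neither indication nor route is named as a category.

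Section 2.2 gives the two treatments as phage therapy (phage treatment group) and standardized non-curative treatment (control group). Phage susceptibility alone decides between them.

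The Conclusions say that the study will "enable us to evaluate the safety profile of the applied phage therapy protocols for three different routes of administration". The Discussion makes the same promise and names the routes as local, topical and intravenous. Section 2.4.2 assigns one route to each disease: local through a drain for MSI, intranasal for CRS, intravenous for sepsis.

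The Assessment of Safety text in Section 2.4.2 calls safety a principal aim. It limits AE collection in general to events directly related to the infection or its treatment. For sepsis it limits recording further, to safety parameters that could in theory be related to phage administration.

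**The concern.** The layout in Section 2.6 and the promise in the Discussion and Conclusions do not match. The abbreviation *i.e.* presents treatment received as the definition of the clinically relevant categories, not as one example of them. With the Section 2.2 definition, that yields a phage column and a control column.

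In such a layout, every variable recorded in more than one disease is combined across diseases. This covers AEs, laboratory tests, demographics and, for MSI and CRS, the PROMIS global health and pain interference scores. For AEs there are two consequences:

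- The figure in each column depends on the share of each disease in that column.
- Sepsis patients enter under a narrower recording rule than the other two diseases, so the numerator does not mean the same thing for all patients.

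What is at stake is the main safety statement. A low pooled AE rate in phage-treated patients could come mostly from the local and intranasal routes and still be taken to cover intravenous use.

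**Working it through.** **1. The plan's own figures.** Section 2.3.1 estimates 150 patients, of whom about 75 will have a positive phagogram: 75/150 = 50%. This is a feasibility estimate from past requests. No alpha, power or effect size is given, so there is no calculation to reproduce.

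**2. The sections side by side.**

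| Question | What the article says | Where |
|---|---|---|
| Breakdown of summaries | Treatment received | 2.6 |
| Meaning of treatment | Phage or standard non-curative | 2.2 |
| Promised result | Safety profile for three routes | Discussion; Conclusions |
| Route and disease | One route per disease | 2.4.2 |
| AE recording | Narrower for sepsis | 2.4.2, Assessment of Safety |
| Main efficacy measures | Specific to each disease | 2.4.2, Assessment of Efficacy |

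Rows 1 and 2 give a two-column table. Row 3 needs the phage column split in three. Row 4 shows that splitting by indication does this exactly. Row 6 limits the point: a disease-free year (MSI), endoscopic and radiological scores (CRS) and delta SOFA (sepsis) are not combined under any layout.

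**3. Dependence on case mix.** A pooled rate is Σ nᵢpᵢ / Σ nᵢ over the three diseases. The article gives neither the split nor the rates, so the values below are illustrative assumptions, in the order MSI, CRS, sepsis.

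Masking, with AE rates of 5%, 5% and 30%:

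- Split 25/25/25: (1.25 + 1.25 + 7.5)/75 = 13.3%.
- Split 45/20/10: (2.25 + 1 + 3)/75 = 8.3%.

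The rate for each route is the same in both lines, but the pooled figure moves by 5 points. Neither figure is close to the 5% or the 30%.

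A false gap between groups, with rates of 5%, 5% and 40% in both groups, so that treatment has no effect:

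- Phage 45/20/10: (2.25 + 1 + 4)/75 = 9.7%. Control 30/20/25: (1.5 + 1 + 10)/75 = 16.7%. Difference −7.0 points.
- Phage 35/20/20: (1.75 + 1 + 8)/75 = 14.3%. Control 45/25/5: (2.25 + 1.25 + 2)/75 = 7.3%. Difference +7.0 points.

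The false gap can take either sign. With equal splits in the two groups it is zero.

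**4. Precision per route.** With zero events in n, the exact (Clopper-Pearson) two-sided 95% upper limit is 1 − 0.025^(1/n). The probability of seeing a 5% event at least once is 1 − 0.95^n. The third column is the exact 95% interval around an observed 20%.

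| n | Upper limit, zero events | 95% interval at 20% | P(at least one 5% event) |
|---|---|---|---|
| 75 (all phage-treated) | 4.8% | 11.6–30.8% (15/75) | 97.9% |
| 25 (assumed, even split) | 13.7% | 6.8–40.7% (5/25) | 72.3% |
| 10 (assumed, small route) | 30.8% | 2.5–55.6% (2/10) | 40.1% |

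Over a wider range of assumed route sizes, the zero-event limit runs from 7.1% (n = 50) to 52.2% (n = 5).

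**The case against.** The best reply is that pooling is inferred. No sentence says that the three diseases will be combined, and Section 2.4 speaks of variables collected for each indication. Treatment received could be stretched to include route. Because route is fixed by indication and indication is recorded, a table by route can be produced at any time. Section 2.6 also warns that results need careful interpretation, and this is a condensed article. Much of this stands: the route profile is left unspecified, and nothing shows that it cannot be delivered. But Section 2.2 makes phage versus control the natural meaning of treatment, and Section 2.6 gives that as the definition of its categories. An analyst who followed the text would not produce the promised result.

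A reader might infer several stronger things that the article does not support:

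- **That efficacy is pooled as well.** The main efficacy outcomes are disease-specific. There is no common one-year success outcome for all 75 phage-treated patients.
- **That the sample-size statement is wrong.** Section 2.3.1 says only "we are unable to perform a power analysis due to the absence of an objective effect size". That is correct, since power needs an effect size. It does not say that precision cannot be calculated.
- **That unlisted confidence intervals or medians are an error.** In a descriptive registry such detail is commonly left to an analysis plan. Intervals are proposed below because they make the precision per route visible.
- **That routes cannot be separated from diseases, and that this is a flaw.** The tie is openly stated, and no comparison between routes is claimed.
- **That case mix will differ between the groups.** It can, because susceptibility decides the group, but the article gives no phage coverage or case mix by indication.

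**Conclusion.** The point holds for AE, laboratory and other shared summaries. The one category named in Section 2.6 does not produce the safety profile by route that the Discussion and Conclusions promise. Read literally, it combines three diseases under two AE recording rules.

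The firm part is the mismatch between sections, which needs no assumption. The size rests on assumptions: the split across routes and all event rates are illustrative, and only the total of about 75 comes from the article. On that basis, the zero-event upper limit of 4.8% for the pooled group becomes 13.7% for a route with 25 patients and 30.8% for one with 10. A difference in case mix alone could create a gap of about 7 points between the groups.

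**What to change.** In Section 2.6, or in the analysis plan that implements it:

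- Make indication (equivalently route) within treatment group the primary layout for AE, laboratory and other shared summaries.
- Report sepsis AEs separately, with a note that they are recorded under a narrower rule.
- Show any pooled safety figure only as a supplement to the tables by indication.
- Give exact (Clopper-Pearson) 95% intervals for AE proportions, so that the precision for each route can be seen.

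No new data are needed, because indication is already recorded. The cost is a change of wording and a few more tables. The downside is that precision per route will look less favourable than the pooled 75 suggests, and a sparsely used route may support only a weak safety statement.

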### 2.7. Ethics and Regulatory Approvals

The study will be conducted in compliance with the principles of the Declaration of Helsinki (2013), the principles of Good Clinical Practice (GCP) and will be in accordance with all applicable regulatory requirements. This protocol and related documents were approved by the Ethics Committee Research UZ/KU Leuven (S64854), in consultation with the Chief Medical Officer and medical board of the University Hospitals Leuven.

The study team shall treat all information and data related to the study as confidential and shall not disclose such information to any third parties or use such information for any purpose other than the performance of the study. The collection, processing and disclosure of personal data, such as patient health and medical information, are subject to compliance with applicable personal data protection and the processing of personal data (General Data Protection Regulation (EU 2016/679)).

### 2.8. Data Handling and Management

Data will be submitted to an electronic Case Report Form (eCRF). Patient data are coded, implying there is a link between the data and the individual who provided it. The subject’s name or other identifiers will be stored separately from their research data and replaced with a unique code to create a new identifier for the subject. The research team is obliged to protect the data from disclosure outside the research according to the terms of the research protocol and the informed consent document.

For this registry-based study, an eCRF will be designed using RedCap to accommodate all study-specific features. Access to the eCRF is password protected and specific functions are assigned (e.g., study coordinator, investigator, monitor). The eCRF is completed in a timely manner after a patient’s visit.

## 3. Discussion

To date, competent authorities in most European countries remain hesitant to implement phage therapy in clinical practice. Despite an increasing number of publications on the topic, this is mainly due to a lack of high-quality safety and efficacy data. Recently, a systematic review regarding the safety and efficacy of phage therapy was performed by our consortium [20]. Although a low rate of adverse events was reported in the included studies, there was a serious discrepancy in the reporting of adverse events between different case studies and even between randomized controlled trials. Furthermore, not all studies described how and if the AEs were collected. In the same systematic review, high efficacy rates were described for all medical disciplines; however, the evidence quality was scored as low to moderate—according to the GRADE (Grading of Recommendations Assessment, Development and Evaluation) approach—due to a heterogeneity between studies. Examples of heterogeneity are different study designs, the use of different administration protocols and the application of personalized phage therapy compared to the administration of fixed phage cocktails [20].

For the abovementioned reasons, the PHAGEFORCE study protocol was developed. To our knowledge, this is the first attempt to set up a standardized, multidisciplinary approach to implement phage therapy in three distinct medical disciplines. By collecting data in a standardized manner, using a patient registry, this study will help evaluate the safety profile of the applied phage therapy protocols for three different routes of administration (i.e., local, topical and intravenous). Preliminary efficacy data will be generated, which can give rise to more insight into the optimal treatment protocol. The creation of this patient registry, which collects information in a standardized way, is an ideal method to characterize the course of the infection, to observe treatment effects and variations in outcome and to identify (risk) factors that correlate with a specific outcome and quality-of-life. Furthermore, our registry is set up in such a way that it will be possible in the future for other centers to join or to combine datasets. The samples that are collected and analyzed will also lead to more insight into the physiology of phage therapy when applied locally, intranasal or intravenously. Further expansion of our phage bank with compatible and ‘in patient-optimized’ phages will be crucial as isolate susceptibility is still a key factor to exclude patients from therapy. A positive feedback loop is generated by embracing longer-circulating phages and observing the consequences of resistance development against phages. This, in combination with co-evolution and machine learning modelling to optimize phage selection and cocktail design, provides a new and integrated approach that has not yet been explored. Furthermore, based on genomic features, we anticipate that novel mechanisms of phage–bacteria interaction will emerge that can trigger further systems biology research.

## 4. Conclusions

In conclusion, for the first time, the PHAGEFORCE study will enable us to evaluate the safety profile of the applied phage therapy protocols for three different routes of administration. Together with the efficacy data that will be collected, this can act as the foundation for future clinical studies. From a molecular microbiology perspective, this study will help us gain insight into phage–bacteria interactions and optimize future phage selection and cocktail design.

## Figures and Tables

**Figure 1 viruses-13-01543-f001:**
[figure not shown]
Flowchart of the PHAGEFORCE study. Patients are screened for eligibility by the CBL. Based on the availability of active phages, the patient can (phage treatment group) or cannot (control group) be treated with phage therapy. Regardless of which group the patient is in, all data related to the infection will be collected. CBL: Coordination group for Bacteriophage therapy Leuven; QAMH: Queen Astrid Military Hospital.

**Figure 2 viruses-13-01543-f002:**
[figure not shown]
Depending on the result of the phagogram, the patient will follow either the phage therapy trajectory (green) or the control trajectory (orange). For each trajectory, there is a standard-of-care protocol. CBL: Coordination group for Bacteriophage therapy Leuven.
